### Study processes – DOORS-M

The schedule of enrolment, interventions and assessment for DOORS-M are described in Fig 2.

**Fig 2 pone.0339336.g002:**
[figure not shown]
Participant timeline: Schedule of enrollment, interventions, and assessments for DOORS-M study.

Potential participants will be identified through their clinical care team, screened, and if eligible approached by a member of the research team for recruitment. Once recruited, information will be collected on a CRF to collate information on the patient’s demographics, previous medical history and sarcoma diagnosis/treatment. Tumour blocks from previous diagnostic or treatment biopsies will be requested for DNA extraction and WES, unless previously sequenced as part of the patient’s clinical care. A blinded pathological review will be undertaken by the study pathologist to confirm the diagnosis. Pre-operative imaging will undergo a blinded review following the same process outlined in DOORS-D, and representative images stored for future AI analysis. At recruitment the participant will have 20mls of blood collected for processing into plasma and storage for ctDNA analysis. Given the constant advances in the field we have not predetermined *a priori* the ctDNA analysis technique. Further blood samples will be collected at subsequent clinic appointments, or 3–6 monthly, for as long as the patient remains within the study. Only participants recruited at the University Hospitals of Leicester will undergo blood sampling due to logistic and financial constraints however, participants will consent to analysis of archival tumour tissue for DNA extraction, thereby expanding the number of sarcoma cases available for analysis. Recruitment from other sites will also involve CRF completion and participant interviews, thereby extending the geographical spread of the study. As with DOORS-D, a subset of participants will be recruited for a semi-structured qualitative interview to discuss their opinions and the potential psychological implications of using ctDNA to diagnose, and/or predict, sarcoma recurrence. The selection of participants will aim to capture a range of opinions and experiences and include an ethnically and socioeconomically diverse population.

### Safety considerations

The DOORS-D and DOORS-M studies are data/sample collection studies and the only physical study procedure participants will be undertaking is venepuncture. The qualitative interview may bring up upsetting memories and participants will be advised that they may choose not to answer a question if they do not wish to. The research team undertaking the interviews are experienced in conducting interviews with oncology populations, following a distress protocol when indicated, supporting participants, and signposting to additional support in order to minimise any distress, including clinical nurse specialists and cancer charity support. Should analysis of a participant’s tumour, radiology, and/or ctDNA result in the identification of an abnormality or genetic mutation that could impact the patient, or their family members, for example BRCA mutations or Lynch syndrome, this result will be communicated to the patient’s clinical care team for onward investigation and if advised further investigations or referrals.

### Analysis

Data from the two studies will be collected from all the participants using the CRFs and descriptive statistics used to report patient demographics and tumour subtype characteristics. Missing data will be minimised by making efforts to ensure complete follow-up. Given the study design all available data will be included and participants will be censored at their last clinic appointment. Correlation between the second pathology and radiology reviews and the patient’s original diagnosis will be undertaken (kappa coefficient). Genomic and/or methylation profiles generated from the study data will be descriptive. Descriptive statistics will be used to report the sensitivity, specificity and diagnostic accuracy of ctDNA and large language model analysis of radiological images to differentiate uterine sarcomas from uterine fibroids. The qualitive interviews will be analysed using a reflexive thematic analysis, as described by Braun and Clarke [37].

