## Abstract

Uterine sarcomas can be difficult to differentiate from uterine fibroids due to many shared symptoms and imaging features, which can result in delayed or missed diagnosis, or over treatment. The ‘Development of a blood test for uterine Sarcoma – Diagnosis’ (DOORS-D) (ISRCTN14800787) and ‘Development of a blood test for uterine Sarcoma – Monitoring’ (DOORS-M) (ISRCTN14174468) studies aim to explore the role for circulating tumour DNA (ctDNA) to diagnose and to monitor uterine sarcomas. DOORS-D will recruit patients who have a suspected uterine sarcoma or large fibroid and are due to undergo surgery (hysterectomy or myomectomy) for a blood sample prior to surgery whereas DOORS-M will recruit patients who have been diagnosed with a uterine sarcoma in the previous 10 years for longitudinal blood sampling every 3–6 months over the course of the study. Information will be collated on patient characteristics and symptoms, tumour characteristics and diagnostic imaging, with representative images selected and analysed using large language models. Analysis of genomic/methylation profile of ctDNA samples collected from DOORS-M will be used to design a ctDNA-based ‘test’. Analysis of the samples collected from the participants recruited to the DOORS-D study will enable the accuracy of the ‘test’ to differentiate uterine sarcomas from fibroids to be determined. In addition, the opinions of patients with a suspected or confirmed sarcoma will be explored through semi-structured qualitative interviews. Purposeful recruitment strategy will ensure that the experiences of women from diverse socioeconomic, cultural and ethnic backgrounds are included. The results of the studies will be shared through conference presentations and peer-reviewed publications.

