### Sample size

DOORS-D and DOORS-M both aim to recruit 50 patients. Sample size calculations for DOORS-D have determined that for a cohort of 50 patients a 40% prevalence of uterine sarcoma (20 cases) would give a 95% confidence interval of width 0.247 for a sensitivity of 0.95 (95% CI: 0.751–0.999). DOORS-M aims to recruit 50 patients with a previous diagnosis of uterine sarcoma. Given the high rate of uterine sarcoma recurrence, recruitment will be achievable within the study duration, given that the University Hospitals of Leicester currently discusses more than 50 patients with ‘suspicious looking fibroid, sarcoma cannot be excluded’ in the multidisciplinary team meetings per year of which 7–10 are confirmed to be a sarcoma on histology examination.

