### Study population

DOORS-D will recruit women due to undergo surgery, either hysterectomy or myomectomy, for a suspected uterine sarcoma or a fibroid, whereas DOORS-M will recruit patients who have already received a uterine sarcoma diagnosis within the previous 10 years. Adult females aged 18–99 years, who meet the above criteria, are willing and able to consent to participate in the trial, and understand study requirements, with interpreter support if needed, will be offered recruitment.

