**Fig 1 pone.0339336.g001:**
[figure not shown]
Participant timeline: Schedule of enrolment, interventions, and assessments for DOORS-D.

Participants recruited to DOORS-D study will have a Case Report Form (CRF) completed detailing their demographic characteristics, medical history, and current clinical episode. Pre-operative radiological imaging, including ultrasound scans, CT/MR/PET scans will undergo a blinded review by the study radiologist, and representative images selected for future AI analysis. The analysis plan using radiomics and large language models has not been determined *a priori* due to rapid changes within the field. Prior to surgery 20mls of blood will be collected, processed into plasma and stored for batched ctDNA analysis. The histological diagnosis from surgery will be classified into 1) uterine fibroid; 2) uterine sarcoma; or 3) smooth muscle tumour of uncertain malignant potential (STUMP). A blinded pathological review will be undertaken by the study pathologist to confirm the diagnosis. Participants diagnosed with a sarcoma or STUMP will be offered recruitment to the DOORS-M study. DNA will be extracted from pathology blocks, either fresh or formalin fixed, for whole exome sequencing (WES). Following surgery, a subset of participants will be invited to an interview to discuss their experiences of the study. Recruitment will be purposeful in order to ensure a breadth of opinions from participants from diverse age, socioeconomic and ethnic populations. The interviews will be transcribed verbatim using Microsoft Teams and will be analysed using a reflexive thematic analysis, as described by Braun and Clarke [37].

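### As written, the ctDNA and image decision rules can be chosen on the same DOORS-D patients whose sensitivity and specificity are then reported, which biases those figures upward

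*Protocol article*

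**What the plan says.** For ctDNA, the Abstract describes two stages. In the first, "ctDNA samples collected from DOORS-M will be used to design a ctDNA-based ‘test". In the second, "Analysis of the samples collected from the participants recruited to the DOORS-D study will enable the accuracy of the ‘test" to be determined.

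Other sections bear on whether that separation holds:

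- **Population.** Under Study population, "DOORS-M will recruit patients who have already received a uterine sarcoma diagnosis within the previous 10 years". Fibroid patients are enrolled only in DOORS-D.
- **Crossover.** Study processes – DOORS-D says participants found to have a sarcoma or STUMP are offered entry to DOORS-M.
- **ctDNA method.** Study processes – DOORS-M says "Given the constant advances in the field we have not predetermined" the ctDNA technique.
- **Image method.** Study processes – DOORS-D says "The analysis plan using radiomics and large language models has not been determined" in advance.
- **Timing.** DOORS-D plasma is stored and assayed in batches. Study timelines expects the genomic and image results only after recruitment ends.
- **Reporting.** The Analysis section says "Descriptive statistics will be used to report the sensitivity, specificity and diagnostic accuracy of ctDNA and large language model analysis of radiological images", for separating sarcomas from fibroids.
- **Precision.** Sample size assumes that 20 of the 50 DOORS-D patients (40%) have a sarcoma, and says this "would give a 95% confidence interval of width 0.247 for a sensitivity of 0.95 (95% CI: 0.751–0.999".

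**The concern.** Sensitivity and specificity are unbiased when the rule was fixed before the scored patients were seen. If the assay, feature or cut-off is picked because it separates those same patients well, part of the apparent separation is chance, and the figures are too high.

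The design leaves room for this. A sarcoma-only cohort can suggest a signature, but it cannot show how often that signature is positive in fibroids. The question is a live one, because the Introduction reports that 40–50% of fibroids have detectable chromosomal abnormalities. By the time the batched assays are analysed, most or all DOORS-D histology will exist. The Discussion foresees a larger later trial of the test. Inflated figures from DOORS-D would feed the decision on whether and how to run it.

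**Working it through.** **1. Can development and evaluation share patients?**

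| Element | ctDNA | Image analysis |
|---|---|---|
| Stated development set | DOORS-M (Abstract) | none stated |
| Stated evaluation set | DOORS-D (Abstract) | none stated separately from development |
| Fibroids available for development outside DOORS-D | none named | none named |
| Method fixed in advance | no | no |
| Lock before linkage to histology | not stated | not stated |

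Even under the Abstract's scheme, a DOORS-D sarcoma or STUMP patient who joins DOORS-M can sit in both sets. Study design also gives the DOORS-M signatures a different purpose, namely detecting or predicting recurrence.

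**2. The plan's own precision figure**

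Inputs from Sample size: 50 × 0.40 = 20 sarcomas, and 0.95 × 20 = 19 detected. The exact (Clopper-Pearson) 95% limits are:

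- lower = Beta quantile(0.025; 19, 2) = 0.7513
- upper = Beta quantile(0.975; 20, 1) = 0.9987
- width = 0.2475 (0.24747 before rounding)

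This reproduces 0.751–0.999 and 0.247. The Wilson (0.764–0.991) and Wald (0.854–1.046) intervals do not. The exact interval treats the 20 results as independent trials of a rule that was already fixed.

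**3. Size of the bias if the rule is tuned on the scored patients**

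From the documents: 20 sarcomas, and 50 − 20 = 30 others, all treated here as fibroids. Assumed, because the documents give no figure: the true AUC, normally distributed markers, independent candidates of equal AUC, and a cut-off that maximises sensitivity + specificity − 1 (Youden's index).

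The fibroid marker is N(0,1) and the sarcoma marker N(d,1), with d = √2·Φ⁻¹(AUC). For each candidate the best cut-off c is found on the 50 patients, and the best candidate is kept. True sensitivity at c is 1 − Φ(c − d), and true specificity is Φ(c). There were 2000 replicates for 1 or 5 candidates and 800 for 20. The overstatement is apparent minus true (sensitivity + specificity), computed before rounding.

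| True AUC | Candidates | Apparent sens/spec | True sens/spec | Overstatement of sum | Coverage of exact 95% CI, sensitivity |
|---|---|---|---|---|---|
| 0.80 | 1 | 0.79/0.75 | 0.71/0.71 | 0.12 | 0.95 |
| 0.80 | 5 | 0.85/0.82 | 0.71/0.73 | 0.24 | 0.85 |
| 0.80 | 20 | 0.88/0.86 | 0.70/0.74 | 0.31 | 0.65 |
| 0.90 | 1 | 0.87/0.85 | 0.80/0.81 | 0.10 | 0.96 |
| 0.90 | 5 | 0.92/0.90 | 0.80/0.82 | 0.20 | 0.88 |
| 0.90 | 20 | 0.95/0.93 | 0.79/0.83 | 0.26 | 0.72 |
| 0.95 | 1 | 0.92/0.90 | 0.87/0.87 | 0.09 | 0.97 |
| 0.95 | 5 | 0.96/0.94 | 0.86/0.88 | 0.17 | 0.92 |
| 0.95 | 20 | 0.98/0.97 | 0.86/0.88 | 0.21 | 0.85 |

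In the row for AUC 0.90 and 20 candidates, the apparent sensitivity equals the planning value of 0.95 while the true sensitivity is 0.79. With one marker the point estimates are biased but coverage stays near nominal. Coverage is lost once several candidates are searched.

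**The case against.** A reader might infer that the cut-off *must* be chosen on DOORS-D, since DOORS-M holds no fibroids. The documents do not support that. No section says so, and for ctDNA the Abstract says the opposite. A rule could be set without DOORS-D fibroids, for example from an assay detection limit, the presence of a sarcoma signature, or outside fibroid plasma. A pre-trained language model that classifies directly may need no fitted cut-off.

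A reader might also infer that plasma calls will use each patient's own tumour sequence, giving a test that could not exist before surgery. The article says only that tumour blocks undergo exome sequencing, not that plasma calls will be tumour-informed. Blinding is stated for the radiology and pathology reviews but not for the ctDNA or model calls, so a safeguard is worth stating. There is no error to allege.

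Further points on the other side are fair. The article is condensed, and a fuller plan may contain internal validation. Reporting accuracy descriptively does not exclude a locked rule. DOORS-D is called a case series, and the Discussion leaves diagnostic ability to a larger later study. The size of the bias rests on assumed inputs, and correlated candidates would give less optimism than independent ones.

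These points remove the word 'must' and moderate the harm. They do not remove the risk. The point does not rest on silence alone: the article affirmatively leaves both methods open, allows crossover into the development cohort, and states a precision figure that assumes a fixed rule.

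**Conclusion.** The concern holds in limited form. As written, the decision rule and cut-off can be chosen on the DOORS-D patients whose accuracy is reported, and nothing stated prevents it. The Abstract's two-stage scheme is only a partial safeguard: it covers ctDNA alone, its development set has no fibroids, and that set may include DOORS-D participants.

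If tuning does occur, the bias is upward. At 20 sarcomas against 30 fibroids and true AUC 0.80–0.95, it is about 0.1 on sensitivity plus specificity with one marker and about 0.2 to 0.3 with the best of 20. The direction is firm. The size depends on the assumed AUC, marker distribution, cut-off rule and number of candidates. The interval in Sample size is guaranteed only for a rule fixed in advance. The plan should be changed, but the design is not invalidated.

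**What to change.** 1. **Lock before linkage.** State that the assay, features and cut-off for ctDNA, and the model, prompt and decision rule for images, are fixed and dated before any DOORS-D result is linked to histology. This still lets the team choose the technique late, which is why it was left open. Exclude DOORS-D participants who join DOORS-M from the development set.
2. **If features or cut-off are instead chosen on DOORS-D,** make the headline sensitivity and specificity cross-validated or bootstrap-corrected, with all computational feature and cut-off selection repeated inside each fold or resample. The choice of laboratory assay need not be repeated: running every candidate assay on one 20 ml draw per participant would not be cheap. Label uncorrected figures 'apparent'.
3. **Blind the calls.** Make each DOORS-D plasma and image call without that participant's histology or tumour sequence.

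The cost is a paragraph of text and some extra analysis work, and reported accuracy will be lower and slightly more variable. Excluding crossovers shrinks the development set. If all 20 planned sarcomas joined DOORS-M and counted towards its 50, then 50 − 20 = 30 would remain for development.

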### Study timelines

The studies opened at the University Hospitals of Leicester on 14/07/2025 and will continue recruiting until 29 February 2028. Results from the qualitative study will be expected after 1 year of recruitment, whereas the results from the AI analysis of radiological imaging and genomic analysis will be expected following completion of recruitment.

## Discussion

The DOORS-D and DOORS-M studies aim to explore the potential of a ctDNA-based approach to uterine sarcoma management and have the potential to give greater insights into the landscape and challenges of differentiating uterine sarcomas from uterine fibroids. Each study aims to recruit 50 patients, to attain 20 sarcoma cases (40% prevalence) in DOORS-D and 50 cases in DOORS-M. Although this is a large number of cases for a rare malignancy, there is the possibility that our cohort may not include rarer subtypes. The developed ctDNA test through these studies would be trialled in a larger uterine sarcoma population, thereby determining diagnostic ability and enabling test modification. Such an approach has been explored previously [24] however, as yet there is no test that can be used in everyday clinical practice to guide patient management. Also, there is a need for greater understanding of the genomic landscape of sarcomas from women of Black ethnicity to ensure that any test that is developed has equitable diagnostic accuracy, unlike other tests currently used to diagnose endometrial cancer, for example the transvaginal ultrasound scan which has a lower diagnostic ability in women of Black ethnicity [38]. The studies include qualitative interviews to ensure that patients’ voices and opinions are heard and are able to contribute to the future development of blood test diagnosis or monitoring for uterine sarcomas. In addition, exploration of opinions and experiences of women from ethnic minority populations is essential in determining the potential impact for such a ‘test’ due to the significantly poorer long-term uterine cancer survival rates [39] and greater prevalence of uterine fibroids [7]. Previous work that the research team has undertaken, identified a lack of awareness of uterine malignancy amongst women from Black ethnic populations resident in England [40] and although efforts are being undertaken to raise awareness of the signs and symptoms of uterine cancer [41, 42], these focus typically on the symptom profile associated with endometrial cancer rather than uterine sarcomas.

There is a clear need to avoid undertreatment and potentially disseminating surgical procedures, however, this needs to be balanced with patients’ wishes for fertility preservation, especially in younger women [11]. One of the main challenges is that over half of patients diagnosed with an unexpected uterine sarcoma are pre-menopausal and/or under the age of 50 years, and the common presenting symptoms, irregular uterine bleeding, pelvic mass and menorrhagia, are indistinguishable from symptoms associated with uterine fibroids [5]. A percutaneous core needle biopsy is routinely performed to diagnose suspected soft-tissue sarcomas [43] however, this is an invasive procedure and although the reported dissemination rate is low for retroperitoneal sarcomas [44] there is no data for uterine sarcomas. It also would require a suspicion of sarcoma and therefore may not impact unexpected cases. It also requires clinicians with the relevant skills to perform the procedure, which is unlikely to be available at every hospital, thereby requiring the patient to travel to a centre with the necessary expertise. The potential of a ctDNA test that would negate the need for a biopsy and could reduce the duration of the patient’s diagnostic pathway. In addition, genomic information on an individual’s sarcoma could potentially be used to guide their management, particularly for immunotherapy, since a number of uterine sarcomas have been identified as having microsatellite instability (MSI) or deletions of *PDCD1*, which encodes PD-1, as well as other actionable mutations such as in *BRCA2* (5%), *BRAF* and *ALK* fusions [22, 45].

Although features associated with uterine sarcomas have been described radiologically [46], the accuracy of differentiating sarcomas from degenerating uterine fibroids using morphological features on MRI is variable, even by expert radiologists [47], sensitivity 70.7% and specificity 76.2% [20]. Radiomic analysis of radiological images may improve diagnostic accuracy with imaging [48, 49] and help reduce intra-observer variability.

In conclusion, the DOORS-D and DOORS-M studies aim to add to the genomic data on uterine sarcomas from a diverse ethnic population, the challenge of correctly differentiating uterine sarcomas from uterine fibroids, and exploring the experiences and opinions of patients who have undergone surgery for a suspected or are confirmed to have a uterine sarcoma.
